## Methods

### Participants and recruitment

The study will be conducted between June 2024 and June 2027 in Germany. It is a part of the transregio (TRR 265) project “Addiction research consortium: Losing and regaining control over drug intake” in Germany.^
40
^ The TRR265 cohort targets 900 people with mainly mild to moderate AUD and 150 age-matched controls. To test causality in real-life mechanisms of problematic alcohol use, we will target 180 risk and/or binge drinkers aged 18 to 70 who report feeling lonely and are craving alcohol. Exclusion criteria include chronic obstructive pulmonary disease, coronary heart disease, heart failure, a body mass index of ≥35 or ≤18, use of assistive devices like walkers, and pregnancy. The target sample will be recruited and screened both from TRR 265 cohort and the general population in Germany. With the assistance of the professional recruitment agencies, we will deploy advertisements across multiple media channels, including newspapers, social media platforms, notice boards, and within both inpatient and outpatient clinics. Participants will receive a monetary reward as compensation after completing the study. The amount of compensation is determined by a percentage of the completed study items.

Risky alcohol use and binge drinking are defined by the German Federal Centre for Health Education (Bundeszentrale für gesundheitliche Aufklärung, BZgA),^
41
^ and the German Ministry of Health.^
42
^ For men, binge drinking is defined as consuming five or more drinks on a single day, while risk drinking is exceeding 14 drinks per week over the past 30 days. For women, binge drinking is consuming four or more drinks on a single day, and risk drinking is exceeding seven drinks per week within the past 30 days. For calculating alcohol consumption, we will ask participants for their sex assigned at birth. Participants will be presented with a list of common alcoholic beverages,^
43
^ and will be asked to report the number of each type of beverage they consume on a weekly basis.^
44
^

For screening purposes, high trait loneliness will be assessed by using the short eight-item form UCLA Loneliness Scale (ULS-8; cutoff scores ≥ 16).^
45
^ High trait alcohol craving will be assessed by using the five-item Penn Alcohol Craving Scale (PACS-5; cutoff ≥ mean from a pilot sample of 50 participants).^
46
^ We will also assess their sociodemographic characteristics (i.e. age, gender, education level, and income), alcohol consumption, mental health status, and cognitive performance.

### Ethics and informed consent

The study will be conducted in accordance with the Helsinki Declaration of 1975 and the ethics committee's standards. The study was evaluated by the Ethics Committee at Charité—Universitätsmedizin Berlin (reference number: EA1/270/22) and at Heidelberg University (reference number: 2023-536). Written informed consent will be obtained from all participants before they start the study.

### Sample size and power considerations

Our power estimation is based on simulation studies for the WPED.^
21
^ We expect a compliance rate exceeding 70% with three (non)encouragements provided daily. Previous research indicates that average compliance rates in similar studies can reach up to 84%. However, many studies with lower compliance rates often remain unpublished.^
47
^ In addition, earlier studies report compliance rates ranging from 50% to 90%.^
48
^ Given this variability, we have adopted a balanced assumption of a 70% compliance rate. In addition, the dropout rate for technological-based psychological intervention varies widely, from 2% to 83%.^
49
^ We also take a balanced approach by assuming a 20% dropout rate.

The study will involve 21 intervention days, resulting in a maximum of 63 intervention data points per person. At a total recruitment of 180 participants and a resulting sample size of *n* = 144 participants subsequent to a 20% drop-out would result in a total of 6350 data points at a compliance of 70% (144 participants × 21 intervention days × 3 (non)encouragements × 0.7 compliance rate). According to Schmiedek and Neubauer's power simulation studies for WPEDs,^
21
^ our sample size will allow for sufficient power to detect a small- to medium-sized average treatment effect across a broad range of conditions.

### Design and procedure

To design the real-life intervention platform, we will combine JITAIs as smartphone applications (apps) with EMA (including physical activity tracking via accelerometers and electronic diaries). For this purpose, we will use the software *movisensXS* and *TherapyBuilder* (both *movisens* GmbH, Karlsruhe) to incorporate two JITAIs including cognitive reappraisal and physical activity, and an active control condition involving a working memory task.^
50
^ In particular, we will generate motivators to break up sedentary phases and to increase the number of steps taken.

We will employ a WPED with counterbalancing. All participants will take part in three conditions in a counterbalanced order, with each participant randomly assigned to receive one of the following: Intervention 1, involving cognitive reappraisal; Intervention 2, which includes physical activity; or an active control condition featuring a gamified working memory task. The duration of each condition will be approximately 6 min. All participants will start with a baseline EMA for seven consecutive days (eight times per day), followed by a 21-day JITAI (three times per day), while also receiving the usual EMA eight times per day. They will end up with a follow-up EMA for seven consecutive days (eight times per day; see Figure 2).

**Figure 2. fig2-20552076241311731:**
[figure not shown]
Experimental design. After initial screening and baseline measurements, a 1-week preintervention ambulatory assessment procedure will be followed by 3 weeks of WPED including JITAIs and subsequent 1-week postintervention EMA. Follow-up measurements will be conducted 12 weeks after the EMA procedure. WPED: within-person-encouragement-design; JITAI: Just-In-Time-Adaptive-Intervention; EMA: ecological momentary assessment.

Two fixed-time EMAs will be administered daily: the first in the morning at 08:00 and the last in the evening at 22:00. The morning EMA will include questions about sleep quality.^
51
^ During the evening EMA, participants will complete a brief 3-min gamified response inhibition task,^
50
^ developed based on the widely used stop signal task. This task is designed to assess potential changes in cognitive functions over time and examine the mediation effects of JITAI on enhancing cognitive function in relation to problematic alcohol use. In addition to two fixed EMAs, eight randomly timed EMAs will be send each day between 08:00 and 21:00, with at least a 60-min interval between them. Participants can delay their responses to the EMAs by up to 60 min to ensure data collection, especially if they are in situations where using their phone is not feasible. If a participant does not engage with the intervention within the 60-min window, we will still send a questionnaire asking about their experienced loneliness and craving, and reasons for skipping the intervention.

At the end of the 21-day JITAI study, we will evaluate participants’ perceptions of the interventions using the Acceptability E-scale^
52
^ the Digital Working Alliance Inventory,^
53
^ and a modified six-item Intervention-elicited Reactance Scale.^
54
^ Moreover, to evaluate the long-term effects, we will conduct follow-up assessments three times 1 month apart (i.e. 1 month, 2 months, and 3 months later). Figure 3 provides a graphical overview of the project.

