^ In essence, JITAIs use real-time analyses to determine momentary states (e.g. EMA of loneliness and alcohol craving and device-based read-outs, such as acceleration signals for physical activity detection), and controlled or randomized intervention-assignments (e.g. an instruction to engage in physical activity after a couple of high-craving ratings). However, experimental manipulations may be infeasible in everyday life due to practical or ethical reasons (e.g. participants may be unable to interrupt their task to follow intervention-instructions under high work-related stress).

Here, the Within-Person-Encouragement-Design (WPED)^
21
^ offers a viable solution through three key elements: (1) smartphone-based, randomly assigned encouragement to engage in an intervention as an instrumental variable (Encouragement), (2) the intervention (i.e. cognitive reappraisal, physical activity) itself (Treatment), (3) target variables (i.e. loneliness and alcohol craving) that are to be causally influenced by the Treatment (Outcome). Based on an instrumental variable estimation approach, a causal treatment effect on the outcome can be analyzed if a correlation between the encouragement and the treatment is present and given the theoretical assumption that any encouragement effects on the outcome are fully mediated by the treatment. The WPED combines three major approaches: (1) multilevel analyses of within-subject mechanisms, (2) experimental within-subject manipulation of the “treatment” variable, and (3) randomized encouragement as an instrumental variable to induce exogenous experimental variation if consistent adherence to the “treatment” is not realistic.

Both cognitive reappraisal and physical activity have been associated with reduced loneliness and alcohol craving.^22–26^ At the behavioral and neurobiological levels, both can improve cognition functions.^27,28^ However, they are very different in nature: on the one hand, cognitive reappraisal is a collection of “structured, goal-directed, and collaborative intervention strategies that focus on the exploration, evaluation, and substitution of the maladaptive thoughts, appraisals, and beliefs that maintain psychological disturbance.”^
29
^ In the context of AUD, at low engagement in reappraisal, greater startle reactivity to uncertain threat was associated with greater problem alcohol use.^
30
^

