### Data analysis

We will analyze the resulting ILD using structural equation and multilevel modeling (MLM) with *R and Mplus*. The procedure including data preprocessing, analysis, and modeling is more detailed below. To preprocess EMA data, we will follow established state-of-the-art procedures detailed in methods guidelines.^
12
^ Physical activity data will be preprocessed by computing established metrics such as MAI and merged with the e-diary data (software Data Merger, *movisens* GmbH, Karlsruhe).

To assess the effectiveness of our interventions (i.e. cognitive reappraisal and physical activity) in reducing loneliness and cravings, we will employ instrumental variable estimation and build two-level structural equation models for path analyses,^
21
^ illustrated in Figure 5. On the first level (Level 1), we will estimate repeated measurements within subjects. In the path analyses, we will model (i) direct effects of the instrumental variable (encouragement for intervention) on the treatment (cognitive reappraisal and physical activity); (ii) the treatment effect on the target/outcome variables (i.e. loneliness or/and alcohol craving); and (iii) the residual (co-)variances (σ^2^_T_, σ^2^_0_, ψ_T0_) of the treatment (е_T_) and outcome (е_O_) on the within-subject level. On the second level (Level 2), we will estimate between subject differences in means, intercepts, and regression coefficients as random effects. Beyond two-level structural equation models, we will use established MLM procedures to test for within-subject changes in alcohol consumption and for pre–post differences in both mean levels of alcohol-use triggers (i.e. loneliness or/and alcohol craving).

For nonsystematic missing data,^
47
^ we will impute the missing values using the standard procedure.^
95
^ Specifically, we will employ the R package Multiple Imputation via Chained Equations to handle missing data through an iterative predictive modeling process.^
14

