^ For the MLM and multilevel structural equation modeling analysis, we will employ the default FIML/MCM procedure in *Mplus*. In addition, we plan to explore the effects of reappraisal and physical activity in comparison to a no-intervention condition within a subsample of participants. The qualitative data will be analyzed using thematic analysis with the software MAXQDA. Our general approach involves identifying, analyzing, and reporting key themes. Specifically, we will read and reread the data to gain a deep understanding, generate initial codes, and group these codes into potential themes. We will then refine and review the themes to ensure they accurately reflect the data. Each theme will be clearly defined and named, and we will integrate the themes with relevant data extracts for reporting purposes.

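### Outcome capture can depend on the randomised encouragement, and the stated missing-data methods (MICE for nonsystematic gaps, default FIML) do not protect the encouraged-unencouraged contrast against this

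*Protocol article*

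**What the plan says.** Sample size and power considerations (protocol article) sets the planning rate: "Given this variability, we have adopted a balanced assumption of a 70% compliance rate". The section multiplies the number of data points by this rate, so the shortfall is lost data points and not merely low uptake. It comes on top of 20% dropout.

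Design and procedure gives each condition about 6 minutes. It lets participants delay a response by up to 60 minutes and states that, when the intervention is not taken up in that window, "we will still send a questionnaire asking about their experienced loneliness and craving, and reasons for skipping the intervention". The account of the triggers, after the description of the active control, allows up to three trigger situations a day. Two are encouraged, and one serves as control without encouragement.

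Data analysis names the missing-data methods. Imputation by chained equations is offered with the qualifier "For nonsystematic missing data". For the multilevel and structural equation models, "we will employ the default FIML/MCM procedure in" Mplus. The path model in the same section consists of encouragement, treatment and outcome. The section names no other variable for handling missing outcomes and makes no statement about missingness that is systematic.

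**The concern.** FIML and chained equations are unbiased when missingness depends only on variables in the model. With the default set-up, those are the variables of the path model. Two design features make it doubtful that ratings are missing alike in encouraged and unencouraged situations:

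- Only the encouraged situation asks for a task of about 6 minutes, so a participant who is busy, stressed or drinking has more reason to let it pass.
- The follow-up questionnaire is described for a skipped intervention. An unencouraged situation has no intervention to skip, so as written the recovery of missed ratings may apply to one randomised state only.

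If the moments without a rating differ in craving or loneliness from those with one, the randomised contrast is taken over differently selected occasions in its two states. This contrast carries hypotheses H1a and H1b. The IV estimate divides it by the difference in uptake, which is below 1, so any bias is enlarged.

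**Working it through.** **1. The plan's own figure.** 180 × (1 − 0.20) = 144 participants. 144 × 21 × 3 × 0.70 = 6350.4, which agrees with the stated 6350. The maximum is 144 × 63 = 9072, so the planned loss is 9072 × 0.30 ≈ 2722 occasions.

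**2. Formula.** Let m be the share of ratings missing and d the gap in SD by which missed ratings lie above answered ones (higher is worse). The full mean is then the answered mean plus m·d. With subscripts 1 for encouraged and 0 for unencouraged:

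bias of the answered contrast = −(m₁d₁ − m₀d₀)

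A negative value favours the interventions. The IV bias is this divided by the uptake difference, which is held fixed here.

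**3. Inputs.** The 2:1 split and the overall 70% are the plan's. The rates by encouragement status, d and the uptake difference of 0.6 are assumptions, because the article gives none of them. Response of 65% and 80% is consistent with the plan: (2 × 0.65 + 0.80)/3 = 0.70.

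**4. Results.**
- Same rate and same gap in both states (m₁ = m₀ = 0.30, d₁ = d₀): bias 0.
- m₁ = 0.35, m₀ = 0.20, d = 0.3: −(0.105 − 0.060) = −0.045 SD; IV −0.045/0.6 = −0.075 SD.
- m₁ = 0.35, m₀ = 0.20, d = 0.5: −(0.175 − 0.100) = −0.075 SD; IV −0.075/0.6 = −0.125 SD.
- Equal rates but unequal gaps (m₁ = m₀ = 0.30, d₁ = 0.5, d₀ = 0): −0.15 SD. Equal response rates alone are therefore not enough; the missed moments must also be alike.

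**5. Effect of the skip questionnaire.** Take the case with d = 0.5, let 65% be the response before the questionnaire, and let it recover 80% of missed encouraged ratings and no unencouraged ones. Then m₁ = 0.35 × 0.20 = 0.07. With the gap held at 0.5 SD, the bias is −(0.035 − 0.100) = +0.065 SD, now against the interventions. If the recovered ratings are a representative draw from the missed ones, the encouraged mean is off by (0.28/0.93 − 0.35) × 0.5 = −0.024 SD and the unencouraged by −0.100 SD, which gives +0.076 SD. Under that second reading the bias vanishes at a recovery r where 0.35r/(0.65 + 0.35r) = 0.15, that is r ≈ 0.33.

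**6. Do auxiliary variables help?** A simulation used 2,000,000 occasions with 2:1 encouragement and no true effect. A latent situation raised the outcome and, where stated, drove non-response. Bias of the contrast in SD:

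| Missing, encouraged/unencouraged | Situation-driven in | Answered only | Plus triggering rating | Plus situation |
|---|---|---|---|---|
| 0.30/0.30 | both | 0.002 | 0.000 | 0.001 |
| 0.35/0.20 | both | −0.058 | −0.028 | 0.002 |
| 0.35/0.20 | encouraged only | −0.147 | −0.070 | 0.000 |
| 0.30/0.30 | encouraged only | −0.127 | −0.060 | 0.002 |
| 0.40/0.10 | encouraged only | −0.168 | −0.080 | 0.000 |

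The triggering rating removes about half of the bias. The rest goes only when the situation itself is in the model. Real proxies for the situation will be less complete than the simulated one.

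**The case against.** The strongest reply is that the skip questionnaire is a safeguard. A skipped intervention with an answered questionnaire is non-uptake with an observed outcome, and using encouragement as an instrument is meant for that. This stands. Only occasions on which the questionnaire is also unanswered have a missing outcome.

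Several stronger readings that a reader might infer also fail:

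- **That the plan declares its missing data nonsystematic.** It restricts imputation to that part and does not address the rest. FIML also allows missingness that depends on modelled variables. This is a gap, not a stated false assumption.
- **That the Introduction admits situation-driven missing outcomes.** It says "participants may be unable to interrupt their task to follow intervention-instructions under high work-related stress". This concerns following instructions, hence uptake. The remark in Design and procedure about moments when a phone cannot be used explains the 60-minute delay, which reduces missing data.
- **That the recorded skip reasons would repair the analysis.** They come from the same questionnaire as the ratings, so they are absent when it goes unanswered.
- **That every comparison is affected.** The working memory control also takes about 6 minutes, so the burden argument does not apply to the interventions against that control. It applies to encouraged against unencouraged situations.

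It can also be said that auxiliary variables and sensitivity analyses belong in an analysis plan that is not shown. That would settle the matter if the article had left missing data open. It names the methods and, for the main models, the software default, so the stated choice can be assessed.

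**Conclusion.** The point holds as a possible bias of unknown direction in the encouraged-unencouraged contrast and its IV estimate. It rests on one feature of the design, that burden and outcome recovery depend on the randomised status, and on the stated reliance on default methods for a planned 30% loss.

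Under the assumed 65% and 80% response and gaps of 0.3 to 0.5 SD, the size is 0.045 to 0.075 SD for the contrast and 0.075 to 0.125 SD for the IV estimate at an uptake difference of 0.6. The article aims at a small to medium effect without a number. If small is taken as 0.2 SD (assumption), the IV bias is 0.075/0.2 ≈ 38% to 0.125/0.2 ≈ 63% of it.

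A reader might infer that the interventions will look better than they are, or that 30% situation-driven non-response is biasing by itself. The documents support neither. The bias is zero when non-response is alike in both states, and the skip questionnaire can turn the sign. The article also expects compliance above 70%, so 30% is a planning figure.

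**What to change.** In Data analysis, replace the default FIML by FIML and chained-equation models with auxiliary variables that are observed even when the outcome rating is missing:

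- the loneliness and craving rating that triggered the occasion, which must have been answered for the trigger to occur;
- accelerometer activity in the response window, where the sensor was worn;
- time of day and weekday;
- ratings and drinks at the next answered prompt.

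The last of these arise after treatment, so they should enter as auxiliaries and not as covariates of the outcome equation.

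Report outcome response by encouragement status and condition, and say whether an unencouraged situation receives an equivalent follow-up rating. Add one delta-adjusted sensitivity analysis that shifts unanswered ratings separately by encouragement status, in both directions. It is needed because the auxiliaries stand in only partly for the situation. Use skip reasons descriptively or to set the range of the shifts.

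The cost is analysis wording, programming, somewhat larger models and one extra sensitivity table. No new data are required.

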**Figure 3. fig3-20552076241311731:**
[figure not shown]
Flow-chart of assessment and intervention.

*Intervention 1 (cognitive reappraisal)*. Cognitive reappraisal describes the process of actively challenging (reappraising) maladaptive beliefs and thoughts associated with distressing mental states, such as loneliness and drug craving.^55–59^ In an initial laboratory session lasting approximately 20–30 min, participants will receive an explanation of cognitive reappraisal and be prompted to identify and challenge thoughts (reappraise) associated with cravings and loneliness. To illustrate the concept of cognitive reappraisal, we developed a comic featuring male and female characters grappling with loneliness and alcohol cravings. This comic was created using the AI image generator Midjourney (see Figure 4). We have a subscription to Midjourney and created Figure 4 on our own using the Midjourney. Participants can access a video illustrating the reappraisal techniques to refresh their understanding of how reappraisal functions (https://www.trr265.org/en/domäne-c05-video).

**Figure 4. fig4-20552076241311731:**
[figure not shown]
Illustrative screenshots from the comic elucidating cognitive reappraisal. This comic was created by us using the AI image generator Midjourney.

The JITAI will take approximately 6 min. It will begin by prompting participants to describe the situations in which they encountered feelings of loneliness or cravings. Subsequently, they will be asked to articulate the thought that most triggers their loneliness or craving. Finally, participants will be tasked with documenting how they challenge this thought, employing four reappraisal strategies.^
60
^ (1) Considering disadvantages: What are the disadvantages of thinking like this if I want to reach my goals to drink less or not to feel lonely. (2) Checking reality: Have I had any experiences to show that this mental statement is not always true? (3) Use other people as a reference point: What would someone who knows to handle this situation well say if they knew I was trying to reduce my drinking/not to feel lonely? (4) Imagine giving advice: What advice could you give to a close person in a similar situation? After each reappraisal, participants will be asked to rate their conviction regarding the thought related to loneliness or craving on a horizontal Visual Analog Scale (VAS)^61,62^ ranging from 0 (“not convinced at all”) to 10 (“strongly convinced”). In addition, they will be prompted to assess the difficulty of reappraising the specific situation using a horizontal VAS ranging from 0 (“strongly disagree”) to 10 (“strongly agree”).

*Intervention 2 (physical activity)*. The physical activity intervention will be designed to increase participants’ step count within a set timeframe. Previous studies have been found that moderate-intensity exercise sessions lasting 5 to 15 min can significantly reduce alcohol cravings.^36,63–65^ Accordingly, our physical activity intervention encourages participants to take a brisk 6-min walk (or engage in indoor walking). During this activity, the number of steps per minute is tracked using a *movisens* Move4 wrist-sensor, providing participants with real-time feedback on their walking pace. Control measures involve automatically assessing the number of steps taken during exercise using the *movisens* Move4 activity sensor.

*Active control (a gamified working memory task)*. The working memory is facilitated by the Great Brain Experiment app,^
66
^ which has been tested and validated in German.^
50
^ The task is gamified to enhance participant engagement and is designed based on a widely used delay-match-to-sample task.^
67
^ For more detailed description of the task, see Brown et al.^
66
^

Randomized encouragement to engage in one of the abovementioned interventions is triggered through *movisensXS*, particularly in contexts where participants’ ratings indicate a high momentary level in at least one of the following target situations: i) high loneliness only, ii) high alcohol craving only, and iii) both high loneliness and craving alcohol. We will limit the number of triggers for interventions to a maximum of 3 per day. While two-third of these situations (*n* = 2), encouragement to engage in an intervention will be provided, the remaining situation (*n* = 1) serve as control condition without encouragement. Loneliness and alcohol craving are detected in real-time via analyses of the participants’ e-diary ratings, and physical activity is monitored via a sensor attached to the participants’ hip (*movisens* move-4), which is connected to the smartphone via Bluetooth low energy for data transfer and real-time analyses. To increase compliance, we will implement a “buffer time” of up to 60 min (see Figure 5).

